## Abstract

**Background:**

Diabetes is the third most common chronic condition in childhood and poor glycaemic control leads to serious short-term and life-limiting long-term complications. In addition to optimal medical management, it is widely recognised that psychosocial and educational factors play a key role in improving outcomes for young people with diabetes. Recent systematic reviews of psycho-educational interventions recognise the need for new methods to be developed in consultation with key stakeholders including patients, their families and the multidisciplinary diabetes healthcare team.

**Methods/design:**

Following a development phase involving key stakeholders, a psychosocial intervention for use by paediatric diabetes staff and not requiring input from trained psychologists has been developed, incorporating a communication skills training programme for health professionals and a shared agenda-setting tool. The effectiveness of the intervention will be evaluated in a cluster-randomised controlled trial (RCT). The primary outcome, to be measured in children aged 4-15 years diagnosed with type 1 diabetes for at least one year, is the effect on glycaemic control (HbA1c) during the year after training of the healthcare team is completed. Secondary outcomes include quality of life for patients and carers and cost-effectiveness. Patient and carer preferences for service delivery will also be assessed. Twenty-six paediatric diabetes teams are participating in the trial, recruiting a total of 700 patients for evaluation of outcome measures. Half the participating teams will be randomised to receive the intervention at the beginning of the trial and remaining centres offered the training package at the end of the one year trial period.

**Discussion:**

The primary aim of the trial is to determine whether a communication skills training intervention for specialist paediatric diabetes teams will improve clinical and psychological outcomes for young people with type 1 diabetes. Previous research indicates the effectiveness of specialist psychological interventions in achieving sustained improvements in glycaemic control. This trial will evaluate an intervention which does not require the involvement of trained psychologists, maximising the potential feasibility of delivery in a wider NHS context.

**Trial registration:**

Current Controlled Trials ISRCTN61568050.

## Background

Diabetes is the third most common chronic disease in childhood, with new cases affecting at least 13.5 per 100,000 children per year in the UK [1]. The incidence has doubled in the last 20 years. To reduce the risk of long-term complications associated with elevated blood glucose (e.g. retinopathy, nephropathy) effective treatment requires regular administration of insulin, most commonly by two to four injections daily in conjunction with a healthy lifestyle. The efficacy of management is monitored in the short-term by regular self-measurement of blood glucose concentrations and in the longer term by monitoring of glycosylated haemoglobin (HbA1c) levels in the blood and regular clinical review in paediatric diabetes clinics.

### Psychosocial aspects of diabetes

It is well recognised [2] that psychosocial and educational influences play a key role in determining management outcomes in children with diabetes. For example, a large audit in Scotland has shown that family structure is associated with glycaemic control throughout childhood [3]. During adolescence, rapid physical change (puberty) leads to relative resistance to the effects of insulin [4]. Concurrent major developmental changes include increasing independence, emerging sexuality and increased stress from peer and academic pressures. These factors together are often associated with deteriorating glycaemic control.

A recent NHS Health Technology Assessment (HTA) systematic review of the effects of educational and psychosocial interventions for adolescents with diabetes reported that there were no results from RCTs of such interventions in the UK [5]. However, the review did identify a study evaluating the effects of Motivational Interviewing (MI) on behaviour change in teenagers. The MI approach focuses on problem solving and goal setting to facilitate behaviour change, and emphasises the importance of using a guiding style of communication when consulting with patients. This trial was based on positive findings from a pilot study in children [6] and an RCT involving adults with type 2 diabetes [7,8]. The findings from this recently completed RCT of MI in children demonstrated persisting improvements in HbA1c up to two years after the start of a one year MI intervention when compared to a group receiving non-specific counselling [9]. Other psycho-educational interventions mostly in a North American context have produced small to medium-sized beneficial effects on a variety of diabetes management outcomes [10]. The HTA review concluded there is a need for well-designed clinical trials that recognise the inter-relatedness of various aspects of diabetes management and assess outcomes specifically targeted for change. In particular, the review recommended that such research be developed through a consultation process with stakeholders including patients, their families, healthcare professionals and health economists. Given the relative scarcity of trained clinical psychologists in paediatric diabetes services [11], this research project has been directed towards developing and evaluating a generic intervention that does not require delivery by trained psychologists. This requirement is emphasised by a more recent review [12] which identified a small number of UK-based studies of psychosocial interventions which have nevertheless been delivered largely by psychologists [6,9,13]. This review also described an ongoing UK evaluation of a family-based educational intervention in children and teenagers with diabetes [14,15].

### Behaviour change: what theory and research tell us

Theories of health behaviour change (e.g. reasoned action theory; the health action process approach) and the research associated with them have clarified the need to look beyond a simple approach to compliance and change based upon the delivery of expert information [16]. As Marteau and Lerman [17] have put it, "Just telling people they are at risk of developing a disease is rarely sufficient to change behaviour". Two variables run through many of the models as predictors of health behaviour change: beliefs about the value of change and beliefs about one's capacity to succeed (self-efficacy). The efficacy of theory-based interventions like cognitive-behaviour therapy have largely been attributed to their capacity to enhance self-efficacy [18]. Using a skills-based approach to counselling has been found to be effective in a number of fields [18,19]. So too, brief interventions have been found to be effective in facilitating change in a number of risky health behaviours [20].

A second line of research has focused on how the therapeutic relationship hinders or promotes motivation to change: an early effort to understand the effective ingredients of MI [21] identified a correlation between confrontational interviewing and resistance, and between "change talk" and behaviour change [22]. A recent meta-analysis of MI [23] found consistent evidence for effectiveness in some (e.g. alcohol, drug use) but not all behavioural domains. Interest in the application of MI in the field of diabetes among young people (predominantly adolescents) has also emerged [6,9,12,13,24]. One of the challenges in much of this research however, has been to specify exactly what elements of a complex method were used by the interventionists. It appears that some of the principles of MI can be realised in brief healthcare consultations, and that helping patients to clarify for themselves why and how they might change their behaviour can be more effective than brief advice-giving [25,26]. This body of work calls attention to both the direction of consultations about change (towards enhancing coping skills) and the way patients are spoken to (eliciting motivation and solutions from them).

### Intervention development

Development of the intervention, subsequently named the 'Talking Diabetes' programme, was informed by the Medical Research Council (MRC) framework for developing and evaluating (non-pharmacological) interventions [27,28]. A number of principles and conceptual aids guided intervention development. Firstly, there was the need to integrate talk about lifestyle change, self-control and quality of life with routine healthcare, where patients are at the receiving end of a range of medical and nursing interventions. Health-care staff need to find ways of moving between providing medical care on the one hand, and "letting go responsibility" on the other [8], to encourage children and teenagers to take control of their health, with assistance from others. During the intervention development stage, a consultative stakeholder reference group considered a consultation model which described the value of moving flexibly between directing, following and guiding *communication styles *when talking about behaviour change. A second conceptual and clinical challenge was the need to move beyond thinking about change as involving an isolated, single behaviour, a limitation in much of the theory of behaviour change in health psychology. The challenge was to help patients find a balance between multiple and inter-related health behaviours and lifestyle choices [5,7,8,29]. Thirdly, targeting or matching interventions to the needs of patients was a design consideration: efforts to match interventions with patients in other fields [30,31] have proved difficult. One approach to targeting was to regard this as something that happens not across interventions but within the consultation, as the practitioner shifts style and topic according to the needs of the patient [32]. To this end, there was some evidence for the acceptability and feasibility of using a targeting approach based on a flexible menu of strategies in which the practitioner and patient select a topic according to need [31,33]. This intervention framework has been developed from efforts to train healthcare practitioners to use elements of MI, and a recent application in drug misuse in young people has produced promising results [34]. In the present context however, it was not the intervention approach (MI) or content that was considered useful, but the use of a framework for targeting within the consultation based on a menu of topics for discussion.

Empirical and consultative work during the intervention development phase helped formulate and operationalise the 'Talking Diabetes' intervention. These activities included: (1) a review of psychosocial and educational interventions for children and teenagers with diabetes; (2) a telephone survey of practitioners (doctors, nurses, dieticians) working in UK paediatric diabetes clinics conducted to explore existing psychosocial practice; (3) a postal survey of UK practitioners exploring experiences and preferences for training in health communication skills [35]; (4) focus groups with young people with diabetes and with their carers; (5) observational work of consultations within three paediatric diabetes clinics in Wales and England; (6) experimental role-play with practitioners and young people; (7) an ongoing stakeholder consultation process built around three one-day workshops attended by teenagers with diabetes, their parents and multi-disciplinary health-care professionals with experience of managing children with diabetes, and (8) local piloting of approaches with young patients. The finalised intervention consists of a blended learning programme for practitioners in the paediatric diabetes field. The programme provides training in a number of communication strategies and skills to help practitioners prepare patients for behaviour change conversations and for conducting such consultations. A key element of this strategic approach was the development of a patient agenda-setting device (3T: TimeToTalk). These development activities will be reported separately.

### The current trial

The development stage provided evidence that the intervention is feasible for teams managing care, and is acceptable to patients and carers. A randomised controlled trial is now needed to test its effectiveness. The primary objective of the trial is to determine whether a multifaceted communication skills training intervention (incorporating a shared agenda setting component) for non-psychologist members of a paediatric diabetes team will improve clinical outcomes (HbA1c) for young people with type 1 diabetes. Secondary objectives include assessing intervention impact upon psychosocial outcomes (including quality of life), and assessing cost-effectiveness. A process evaluation will assess skill retention, competency and confidence of clinical team members in delivering the intervention.

## Methods/Design

### Ethical and governance approval

Multi-centre approval has been granted by Berkshire Research Ethics Committee (07/MRE12/9). Site-specific approval has been granted by local RECs at all trial sites and all participating Acute Trust Research and Development Departments.

### Design

The study is a pragmatic cluster randomised controlled trial (Figure 1). Twenty-six teams will be randomised to receive training at the start (intervention group) or the end of the one-year study period (control group).

**Figure 1 F1:**
[figure not shown]
**Trial structure and outcomes**.

### Sample size

In order for an individually randomised trial to have 80% power to detect a moderate effect size of 0.4 for HbA1c at a 5% significance level, 200 patients would be required. Audit data from a Welsh paediatric diabetes interest group (The Brecon Group) relating to 750 children from all 13 centres in Wales indicates an intra-cluster correlation coefficient of 0.08 for HbA1c in patients aged 4 - 15 years. With 24 centres recruiting an average of 23 patients each, this inflates the total sample size required to 550. To allow for loss to follow-up, the intention is to recruit 700 patients (78% follow-up). Twenty-six centres have been recruited to allow for any subsequent centre drop-out.

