### Analysis

#### Main analysis

The main analysis will be an intention to treat comparison of HbA1c values between the two groups of patients at one year. This will use multi-level modelling to allow for cluster (centre) and individual effects (including baseline concentrations of HbA1c as a covariate). Secondary analysis of other outcomes such as quality of life and cost will also be conducted using multi-level modelling incorporating baseline scores as covariates. A dose-response analysis will be conducted to explore associations between the amount of patient contact and an intervention effect. The two groups will also be compared on the non-attendance rate as the intervention may improve motivation to attend. A review of patient outcome measures used in diabetes, whilst predominantly in adults, concluded that whilst most have been shown to have content validity, there is less available evidence regarding reliability and responsiveness to change [48]. Responsiveness of the specific measures used will be assessed using both effect sizes and correlation to clinical variables and self-rated change.

Competence, confidence and importance of behaviour change counselling will be compared between the two groups at one year using a two level linear regression model controlling for profession. Short and long term impacts of the intervention will be analysed within the intervention group only using repeated measures ANOVA. Analysis of reliability of the competence inventory will be conducted on the trial data.

No formal subgroup analyses are planned. However, exploratory analysis of the impact of patient level factors (e.g. age and gender) and clinic level factors (e.g. size of clinic) on the effect of the intervention will be carried out. No interim analyses are planned.

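### The inflation from 200 to 550 patients makes no allowance for there being only 24 randomised centres: on its own inputs the unadjusted comparison has about 77% power, not 80% (low severity)

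*Protocol article*

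**What the plan says.** The Sample size section of the protocol article works in steps. For an individually randomised trial it states "80% power to detect a moderate effect size of 0.4 for HbA1c at a 5% significance level, 200 patients would be required". Audit data from Wales, it says, "indicates an intra-cluster correlation coefficient of 0.08 for HbA1c in patients aged 4 - 15 years". It then concludes: "With 24 centres recruiting an average of 23 patients each, this inflates the total sample size required to 550". The recruitment target allows for attrition: "To allow for loss to follow-up, the intention is to recruit 700 patients (78% follow-up"). Twenty-six centres were recruited, and the two beyond 24 are described as cover for centre drop-out. The Discussion repeats that purpose.

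The Randomisation section allocates centres, half to each arm. The Main analysis section describes the comparison of one-year HbA1c as follows: "This will use multi-level modelling to allow for cluster (centre) and individual effects (including baseline concentrations of HbA1c as a covariate"). The Sample size section mentions neither degrees of freedom linked to the number of centres nor a correlation between baseline and one-year HbA1c.

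**The concern.** Multiplying an individually randomised sample size by the design effect corrects the variance of the treatment difference. It leaves in place the critical value of a trial with about 200 independent patients, roughly 1.96 to 1.97. Because centres are randomised, the between-centre variation has to be estimated from 24 centres, and the critical value for an unadjusted comparison is 2.07 (t on 22 degrees of freedom). The omission makes the stated total optimistic.

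What is at stake is interpretation. A null result will be read against a stated 80% power for 0.4 standard deviations. On the stated inputs the unadjusted 24-centre comparison does not have that power. The analysis that will be run adjusts for baseline HbA1c, and the section gives no assumption from which its power could be worked out.

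**Working it through.** **Inputs from the Sample size section:** effect 0.4 (in SD units), 5% level (taken as two-sided, which reproduces the 200), intra-cluster correlation (ICC) 0.08, k = 24 centres, m = 23 patients per centre. Allocation is 1:1 by centre (Randomisation section). The baseline to one-year correlation r is not in the document and is treated below as an assumption.

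**1. The plan's own figures reproduce.**
- Individually randomised: 99 per arm by the normal formula (198 in total). The two-sample t-test formula gives 99.08, so 100 per arm and 200 in total.
- Design effect = 1 + (23 - 1) x 0.08 = 2.76.
- 198 x 2.76 = 546 and 200 x 2.76 = 552, against 550 stated. Also 24 x 23 = 552.
- 550/700 = 78.6%, in line with the stated 78%.

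**2. Power at 24 x 23, unadjusted.**
- Variance of the difference = 4 x 2.76/552 = 0.0200, so the standard error is 0.1414.
- Noncentrality = 0.4/0.1414 = 2.83.
- Normal reference (critical value 1.96): power 80.7%.
- Noncentral t on 24 - 2 = 22 degrees of freedom (critical value 2.074): power 77.1%. A simulation of centre means (200,000 runs) gave 76.9%.
- 80% power on 22 degrees of freedom needs a noncentrality of about 2.93, so the detectable effect is 2.93 x 0.1414 = 0.415.

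**3. What would give 80% unadjusted, on t with k - 2 degrees of freedom.**

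| Centres x analysed per centre | Analysed | Power |
|---|---|---|
| 24 x 23 | 552 | 77.1% |
| 24 x 29 | 696 | 80.0% |
| 24 x 30 | 720 | 80.4% |
| 26 x 21.15 | 550 | 79.5% |
| 26 x 22 | 572 | 80.0% |
| 26 x 23 | 598 | 80.6% |

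**4. The planned baseline-adjusted analysis at 24 x 23, on t with 22 degrees of freedom, for assumed r.**
- If baseline explains a share r² of the variance at both levels, the variance is 0.0200 x (1 - r²).
- If it explains only within-centre variance, the variance is (4/24) x [0.08 + 0.92 x (1 - r²)/23].

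| Assumed r | Both levels | Within-centre only |
|---|---|---|
| 0.3 | 80.9% | 78.4% |
| 0.5 | 87.7% | 80.6% |
| 0.7 | 96.6% | 84.0% |

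Power of 80% is reached at r of about 0.27 in the first case and about 0.46 in the second.

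**The case against.** The strongest reply is that nothing in the section is miscalculated. Design-effect inflation is standard and correctly carried out, and the document does not say which reference distribution was used. The 77% also needs two conditions together: both spare centres are lost, and the planned covariate is ignored. With 26 centres the unadjusted power is 80% for practical purposes. Leaving a baseline covariate out of a sample-size calculation is a common conservative choice and does not contradict the Main analysis section.

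Most of this stands, and it limits the point. It does not remove it: the section ties its total to 24 centres and reserves the other two for drop-out, so 24 x 23 is the case it claims to have powered.

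A reader might go further in four ways that the document does not support.
- **That the trial is underpowered.** Retained centres and baseline adjustment may each close the gap, and no correlation is given from which a shortfall could be shown.
- **That 550 is an arithmetic slip.** It reproduces.
- **That the primary test will exceed its 5% error rate.** This would follow only if the multilevel model were tested against a normal or chi-square reference. The Main analysis section names no reference distribution, and a condensed article commonly leaves that to the analysis plan.
- **That unequal centre sizes lower power further.** Any figure needs an assumed coefficient of variation, and the target of 30 recruits per clinic is meant to keep sizes similar.

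**Conclusion.** The point holds in a limited form and is of low severity. The step from 200 to 550 omits the centre-level degrees of freedom. On the section's own inputs, unadjusted and with equal centre sizes, power is 77.1%. That is 2.9 points below the stated 80% and 3.6 points below the 80.7% given by a normal reference. As a required total for 80% power with 24 centres, 550 is therefore optimistic by about 150 to 170 analysed patients (700 to 720, less 550).

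This describes the calculation as written and does not predict the power of the trial. Whether the baseline-adjusted analysis reaches 80% with 24 centres depends on a correlation that the document does not give. The threshold is about 0.27 or about 0.46, according to how much between-centre variance baseline HbA1c explains.

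**What to change.** In the Sample size section, restate the power for 24 centres of 23 patients as about 77% for an unadjusted comparison, allowing for centre-level degrees of freedom, and as about 80% if all 26 centres are retained. Then add the power of the baseline-adjusted multilevel analysis. State the assumed correlation between baseline and one-year HbA1c, show a range of values, and say whether baseline is taken to explain variance at both levels or only within centres.

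This changes wording only and needs no extra patients or centres. The one cost is an unadjusted figure about 3 points less favourable. The adjusted figure may well exceed 80%, depending on the correlation assumed.

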### Clinic and patient selection

Potential clinics were approached using a variety of recruitment methods. Flyers outlining the nature of the study were distributed to members of the British Society for Paediatric Endocrinology and Diabetes (BSPED) and consultants and diabetes specialist nurses on a database compiled as a result of the surveys carried out during the development phase. Flyers were also distributed at professional and scientific conferences. Expressions of interest were received from 54 UK clinics. Thirty centres were approached to participate based on clinic size and geographical location: 26 agreed to take part and were able to meet contractual requirements.

All team members undergoing training will be consented prior to randomisation and the incentive of receiving training at the end of the study is provided to avoid differential levels of dropout or engagement between the two groups of teams. Recruitment bias is common in cluster randomised trials [36]. In this study, patients are identified and approached by a specially trained member of the local team (or occasionally a UKCRN research nurse) during the period prior to team randomisation and intervention training. All eligible patients are identified from clinic lists by the research nurse. A random sample of 40 patients will be selected by the coordinating study team (from an anonymised list) and approached en bloc by the research nurse, to obtain a target sample of 30 recruited patients per clinic.

